### 2.6 Drop-out criteria

1) Participants who would develop severe, acute conditions (e.g., diabetic ketoacidosis) or special physiological changes (e.g., state of pregnancy) that are not appropriate for this trial.2) Participants who would show low compliance, such as failing to take their medication regularly or at a rate of less than 80% during the trial.3) Participants who would have taken drugs prohibited by the study protocol.4) Participants who would voluntarily withdraw from the trial at any time according to the informed consent form.

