### 2.10 Sample size calculation

In a previous study (Xu, 2017), JTTF reduced HbA1c levels in diabetic patients with heat stagnation in liver and stomach after 12 weeks of treatment (treatment group: 6.94±0.88%, control group: 7.64±0.72%, mean difference between the two groups: 0.7%). Considering a type I error of 5% (α = 0.05) and a power of 85%, the experimental and control groups were allocated at a ratio of 1:1. The sample size was calculated using Power Analysis and Sample Size (PASS) software (version 15.0); a total of 76 patients will be required. According to the dropout rate of 20%, we set the final sample size to 96, with 48 patients in each group, considering the number of dropout samples.

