## 3 Statistical methods

### 3.1 Data analysis

Data will be analyzed using SPSS software (Version 24.0; IBM Corp. Armonk, NY, United States). Continuous variables will be represented as means, standard deviations, medians, and minimum/maximum values. If the data confirms normal distribution, an independent sample *t*-test will be used to assess the differences between the two groups, and a paired sample *t*-test to compare the differences between groups before and after the intervention. Wilcoxon signed-rank test will be used for data that does not conform to normal distribution. Grade data will be analyzed using Wilcoxon’s signed-rank test or the CMHχ2 test. Statistical significance will be set at *p* < 0.05.

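### Section 2.6 classes low compliance and prohibited-drug use as drop-out; if these participants leave the trial or the comparison, as the sample size allowance suggests, the groups compared are no longer those randomised

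*Protocol article*

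**What the plan says.** Section 2.6 (Drop-out criteria) of the protocol article gives four reasons for drop-out:

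1. Severe acute conditions or special physiological changes such as pregnancy.
2. Low compliance, for example "failing to take their medication regularly or at a rate of less than 80% during the trial".
3. "Participants who would have taken drugs prohibited by the study protocol".
4. Voluntary withdrawal.

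The list does not separate stopping study treatment from leaving the study.

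Section 2.10 (Sample size calculation) states that "a total of 76 patients will be required", and then: "According to the dropout rate of 20%, we set the final sample size to 96", with 48 per group. Section 2.6 is the only place where the article defines a drop-out.

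Section 3.1 (Data analysis) names between-group and within-group tests but no analysis population. Section 2.9 says that the trial is open-label. Under section 2.7 the experimental group takes JTTF twice daily for three months on top of the control treatment, which itself includes oral medication. Table 1 schedules VFA, TCM symptoms and the laboratory safety tests at week 12.

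**The concern.** Low compliance and prohibited-drug use arise after randomisation, and neither prevents a week-12 measurement. Putting them in one list with withdrawal treats participants who could still be measured as if they were lost.

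Treatment can influence both events. Participants and physicians know the allocation. Only the JTTF arm has an extra twice-daily product to keep up, and section 2.8.6 says that it may be associated with mild diarrhoea. The compliance criterion also leaves room for judgement by unblinded staff, because regular intake is not defined and the 80% limit is only one example. Removal can therefore depend on arm and on response.

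Two things are at stake:

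- **Validity of the comparison.** If these participants are left out, a difference in VFA or TCM score mixes the treatment effect with differences in who remained.
- **Data that cannot be recovered.** A statistical analysis plan can name an all-randomised population, but it cannot restore week-12 values that were never collected because participation had ended. The protocol has to settle this.

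**Working it through.** **1. The plan's own figures**

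Inputs from section 2.10: HbA1c difference 0.7; SDs 0.88 and 0.72; α = 0.05; power 85%; 1:1 allocation; 76 required; drop-out 20%; final size 96. Sidedness is not stated, so two-sided is assumed.

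- Drop-out step: 38 / (1 − 0.20) = 47.5, rounded up to 48 per arm, or 96 in total. This reproduces. The allowance is sized so that 38 per arm remain after drop-outs are taken away.
- The 76 itself does not reproduce. Pooled SD = √[(0.88² + 0.72²)/2] = 0.804, and n per arm = 2 × (1.960 + 1.036)² × 0.804² / 0.7² = 23.7, so 24 per arm or 48 in total (50 with the t-distribution). This is a separate matter and does not affect the present point.

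**2. Size of a possible bias**

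Assumptions, none taken from the article: there is no true effect; a share *p* = 0.20 is removed from the JTTF arm only; those removed would have done *d* SD worse than those kept; control losses, if any, are unrelated to outcome. The 20% borrows the article's overall drop-out rate, which covers all four reasons.

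Bias = *p* × *d*, so with *d* = 0.5 it is 0.20 × 0.5 = 0.10 SD.

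Type I error = Φ(bias/SE − 1.96) + Φ(−bias/SE − 1.96), in SD units.

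- Only the JTTF arm shrinks (38 vs 48): SE = √(1/38 + 1/48) = 0.217. Bias/SE = 0.46. Type I error = Φ(−1.50) + Φ(−2.42) = 0.067 + 0.008 = 7.5%.
- Both arms end at 38: SE = √(2/38) = 0.229. Bias/SE = 0.44. Type I error = Φ(−1.52) + Φ(−2.40) = 0.064 + 0.008 = 7.2%.

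Range over the assumed difference, at 38 vs 48:

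| Those removed do worse by | Bias | Type I error |
|---|---|---|
| 0.25 SD | 0.05 SD | 5.6% |
| 0.50 SD | 0.10 SD | 7.5% |
| 1.00 SD | 0.20 SD | 15% |

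If both arms lost the same share with the same difference, the biases would cancel (0.10 − 0.10 = 0). If the selective loss fell on the control arm instead, the sign would reverse.

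**3. Cost in power of keeping everyone**

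With the article's HbA1c inputs and 48 per arm, power is 98.9% for a difference of 0.7. Assume that 20% of the JTTF arm is non-adherent and gets no effect at all. The difference falls to 0.7 × 0.8 = 0.56, SE = 0.804 × √(2/48) = 0.164, and power = Φ(0.56/0.164 − 1.96) = Φ(1.45) = 92.7%. At 10% non-adherence the difference is 0.63 and power is 97.0%. On these inputs no more than the planned 96 is needed. Power for VFA and TCM score cannot be computed, because the article gives no figures for them.

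**The case against.** The strongest objection is that the article never says what happens to the data of drop-outs. It defines no analysis set, does not say that their visits stop, and does not say that their results are discarded. Analysis populations are commonly left to the full protocol or the statistical analysis plan, neither of which is shown. An allowance for drop-out is also routine and does not by itself define who is analysed. This stands. A reader might infer from section 2.6 that the plan compares only adherent completers, but the documents do not say so. What survives is the stated rule: two avoidable losses are written into the definition of drop-out, and the sample size is built as if drop-outs do not count.

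Three further objections stand in part:

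- **Direction.** Control participants also take oral medication and can meet criteria 2 and 3. Controls who are doing poorly may be the ones who seek other drugs, and removing them would work against JTTF. Bias towards JTTF is plausible because of the added burden in that arm, but it is not certain.
- **Safety.** A reader might infer that the rule hides poor tolerability. Section 2.8.6 counts adverse events whether or not related to the study drug and follows all of them until stable or resolved. The documents support only a narrower worry, that scheduled week-12 safety tests could be missed.
- **Magnitude.** The bias figures rest on assumed shares and differences. They illustrate what the rule could do and do not measure a known defect.

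**Conclusion.** The point holds in a conditional form. Section 2.6 classes low compliance and prohibited-drug use as drop-out, and section 2.10 budgets drop-outs as not contributing. If such participants leave the trial or the comparison, as this wording suggests, the groups compared are not those randomised. The possible distortion is moderate: 0.10 SD and a type I error of about 7 to 7.5%, assuming that 20% are removed from the JTTF arm only and would have done 0.5 SD worse. It is near zero if losses are alike in both arms, and larger if those removed differ more.

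The documents do not establish that only adherent completers will be analysed, that the bias must favour JTTF, or that adverse events go unreported. The change should be made, with medium confidence: the rule is explicit, the remedy is cheap, and outcomes that are not collected cannot be restored later.

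**What to change.** - In section 2.6, reclassify criteria 2 and 3 as protocol deviations and not as study drop-out.
- State that these participants still have VFA, TCM score and the scheduled safety tests at week 12 unless they withdraw consent.
- State that the primary comparison includes all randomised participants in their assigned arm, with the set taking at least 80% of medication as a sensitivity analysis.
- Leave criterion 1 and all clinical decisions on stopping treatment as they are.

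The cost is amendment wording and attendance of these participants at a week-12 visit that Table 1 already contains. The estimated effect may be slightly diluted. On the article's HbA1c inputs the planned 96 absorbs this, but the same cannot be shown for VFA or TCM score.

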### 2.7 Intervention

The control group will receive conventional basic treatment, including health education and oral medications to stabilize blood sugar, blood pressure, and lipid levels. Meanwhile, the experimental group will be given JTTF on the top of the control group. In this study, Chinese herbal medicine concentrated granules (CCMG) will be used to replicate the traditional method of preparing herbal tonics by using herbs as raw materials and modern extraction and concentration techniques. All herbal pellets will be manufactured and supplied by China Resources Sanjiu Pharmaceutical Co. and also tested by their quality management department for compliance with the grade standards of the Chinese Pharmacopoeia (2020 edition). Voucher specimens of all drugs are deposited at the Bureau of Traditional Chinese Medicine, Shenzhen Hospital, Guangzhou University of Chinese Medicine (Futian) (Shenzhen, China). The decoction and packing of botanical drugs are uniformly operated by Kangmei Pharmaceutical Co., Ltd. Smart Pharmacy. CCMG is based on the “Research Guidelines for Single Flavor Chinese Medicine Concentrated Granules” and the “Pharmacopoeia of the People’s Republic of China” (2010 edition). Extracted in a fully enclosed pipeline production line in GMP workshop. All herbs are mixed in the proportions described above, steeped in 10 volumes of pure water for 0.5 h, heated to boiling, decocted for 1 h. The water extract is filtered and the residue is then decocted with 8 volumes of pure water for 40 min. The two liquid extracts are combined, settled and filtered, concentrated to a thick paste, and processed into concentrated granules by spray drying. The process parameters are screened by orthogonal design method according to the composition characteristics of different species. A certain amount of soluble dextrin is added as an auxiliary material to assist the molding. The dry extract ratios of the five raw herbs were 1:6 for *Coptis chinensis*, 1:2.4 for *Rheum palmatum*, 1:10 for *Astragalus mongholicus*, 1:6.7 for *Salvia miltiorrhiza* and 1:6 for *Bupleurum chinense*. The final JTTF is made by combining the individual herbal pellets in the leaching ratio, which is equivalent to 64 g of raw herbs. It is packaged with aluminum-plastic-aluminum composite film (BOPP/AL/CPE) packaging material sealed on four sides. Dissolve the concentrated granules in 200 ml of boiling water and take warm. Take twice daily, half an hour after breakfast and dinner. The observation period will be administered for three months.

Both groups will receive the same health education information on diabetes and NAFLD, assistance, lifestyle interventions, and management. It includes developing a diet of low sugar, low fat, and less refined carbohydrates, controlling the intake of total calories in the diet, helping participants to choose appropriate exercise methods, and encouraging patients to remain relaxed and actively cooperate with treatment. Face-to-face nutritional education will be provided at each follow-up visit.

### 2.8 Outcome assessment

#### 2.8.1 Demographic information

All demographic information will be collected at enrollment, including sex, age, course of disease, family history, previous medical history, drug use, smoking, and drinking history.

#### 2.8.2 Primary outcomes

The primary outcome is change in visceral fat area (VFA) and TCM syndromes efficacy score scale. Changes in VFA will be compared between the two groups before and after treatment. The indicator will be tested at baseline and week 12. The TCM symptom scoring standard is presented in Supplementary Material S3.

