## Abstract

**Background:** The incidence of Type 2 diabetes mellitus (T2DM) combined with non-alcoholic fatty liver disease (NAFLD) has risen over the years. This comorbid condition significantly increases the probability of cirrhosis, liver cancer, and mortality compared to the disease alone. The multi-targeted, holistic treatment efficacy of traditional Chinese medicine (TCM) plays a vital role in the treatment of T2DM and NAFLD. Jiedu Tongluo Tiaogan Formula (JTTF), based on TCM theory, is widely used in clinical treatment, and its effectiveness in lowering glucose, regulating lipids, improving insulin resistance, and its pathways of action have been demonstrated in previous studies. However, the mechanism of this formula has not been investigated from a metabolomics perspective. Moreover, high-quality clinical studies on T2DM combined with NAFLD are lacking. Therefore, we aim to conduct a clinical trial to investigate the clinical efficacy, safety, and possible pathways of JTTF in the treatment of T2DM combined with NAFLD using metabolomics techniques.

**Methods:** A total of 98 participants will be recruited to this clinical trial and randomly assigned to either a treatment group (JTTF + conventional basic treatment) or control group (conventional basic treatment) in a 1:1 ratio. Both groups will have received the same lifestyle interventions in the preceding 12 weeks. The primary outcome will be change in visceral fat area and total score on the TCM syndromes efficacy score scale. The secondary outcome will include changes in ultrasound steatosis grade, fibrosis 4 score (FIB-4), metabolic parameters, anthropometric parameters, visceral fat area. In addition, serum and urine samples collected at baseline and at the end of 12 weeks of treatment will be sequentially tested for untargeted and targeted metabolomics.

**Discussion:** This study will evaluate the efficacy and safety of JTTF, as well as investigate the differential metabolites and possible mechanisms of JTTF treatment in T2DM combined with NAFLD. We hypothesize that patients will benefit from JTTF, which may provide strong evidence for the clinical use of JTTF in the treatment of T2DM and NAFLD, leading to the possibility of further mechanistic exploration.

**Clinical Trial Registration:** This clinical trial has been registered in China Clinical Trial Registry (ChiCTR 2100051174).

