#### 2.8.3 Secondary outcomes

1) Changes in hepatic steatosis factors by ultrasound grading of steatosis.2) Changes in metabolic parameters: glycated hemoglobin (HbA1c) levels, fasting plasma glucose (FPG), 2-h plasma glucose (2h-PG), fasting insulin, blood lipids including total cholesterol (TC), triglycerides (TG), high-density lipoprotein-cholesterol (c-HDL), low-density lipoprotein (c-LDL), apolipoprotein A (ApoA), and apolipoprotein B (ApoB).3) Changes in anthropometric parameters: Waist-to-height ratio (WHtR), Body Mass Index (BMI), waist circumference (WC), hip circumference (HC).4) Changes in hepatic fibrosis factors and hepatic function: The changes in Fibrosis 4 Score (FIB-4, http://gihep.com/calculators/hepatology/fibrosis-4-score/) can be calculated by the formula:

$$\mathrm{Age}\;\left(\mathrm{years}\right)\text{x}\;\mathrm{AST}\;/\mathrm{PLT}\;\left(\times 10^{9}/L\right)\text{x}\sqrt{\mathrm{ALT}}$$

The units of measurement for ALT and AST are aligned with those for age and PLT.

Definitions for the following abbreviations: AST: Aspartate aminotransferase; PLT: platelet; ALT: Alanine aminotransferase.5) Changes in visceral fat area.

All measurements will be performed at baseline and at week 12. Additional FPG and blood lipid test will be performed at week 6.

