## 4 Discussion

NAFLD has a high prevalence worldwide, affecting approximately 25% of the population (Younossi et al., 2021). It is extremely harmful, especially when combined with diabetes, and significantly increases the risk of developing cirrhosis and liver cancer as well as the mortality rate (Golabi et al., 2018; Younossi and Henry, 2019). However, there are still no safe and effective drugs for the treatment of T2DM in combination with NAFLD (Ferguson and Finck, 2021). The current first-line interventions for both NAFLD, and T2DM with NAFLD remains lifestyle modification and weight loss, which also has the disadvantages of low compliance and difficulty in long-term implementation. Therefore, there is a need for a protocol that systematically treats T2DM combined with NAFLD as a comorbid disease, while improving clinical symptoms and combining metabolomics to identify targeted pathways of action to regulate glucose and lipid metabolic abnormalities.

This study is a double-armed, parallel-designed, randomized, controlled clinical trial that aimed to verify the efficacy and safety of JTTF for glucose-lowering and lipid-modulation and to investigate the differences in serum and urine metabolites before and after treatment. The proposed protocol combines clinical evaluation with metabolomics in an attempt to determine its mechanism of action and pathway of action, offering the possibility to systematically elucidate the effectiveness and mechanisms of action of JTTF. Considering the limitations of liver biopsy implementation, this study focused on subjects with fatty liver diagnosed by ultrasound to observe changes in visceral fat and subcutaneous fat area. In addition, patients’ blood lipids, liver function, BMI, HbA1c level, blood glucose, TCM symptom scores, and other indicators will be assessed, and the degree of fibrosis and insulin resistance will be evaluated. Disease onset and progression will be comprehensively evaluated in this clinical study.

This study has some limitations. First, coronavirus outbreaks remain a serious concern worldwide and may affect patient follow-up. In addition, this is a single-center study conducted in China; therefore, the generalizability of the findings remains unclear. Finally, the clinical application of JTTF should be expanded to provide evidence for further mechanistic studies.

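### Two primary outcomes have no stated success rule and VFA is ranked both primary and secondary, so the trial's confirmatory claim is undefined

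*Protocol article*

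**What the plan says.** - **Primary outcomes.** Section 2.8.2: "The primary outcome is change in visceral fat area (VFA) and TCM syndromes efficacy score scale". The abstract names the same pair: "The primary outcome will be change in visceral fat area and total score on the TCM syndromes efficacy score scale". In both places a singular noun covers two outcomes joined by a conjunction, with no success rule.
- **VFA as secondary.** Item 5 of section 2.8.3 reads "Changes in visceral fat area". That section measures its outcomes at baseline and week 12, the times at which section 2.8.2 measures VFA. The abstract's list of secondary outcomes ends with "metabolic parameters, anthropometric parameters, visceral fat area".
- **Threshold.** Section 3.1: "Statistical significance will be set at *p* < 0.05". It gives no order or division between the two primaries.
- **Interim look.** Section 3.2 plans one analysis of the primary outcome, again singular, at half enrolment. Its purpose covers efficacy as well as safety, and no boundary is given.
- **Sample size.** Section 2.10 takes its 85% power from HbA1c, which section 2.8.3 lists as secondary.
- **Subcutaneous fat area.** Table 1 schedules it beside VFA, and the Discussion says the study will "observe changes in visceral fat and subcutaneous fat area". No outcome list in section 2.8 or the abstract contains it.

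**The concern.** With two primary outcomes, the success rule determines both the error rate and the claim. Here at least two rules fit the text, and they give different trials. If one significant outcome is enough, there are two chances of a false positive at 0.05. If both are needed, there is no inflation, but the trial is harder to win.

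The choice also affects what a positive result would mean. Section 2.9 describes an open-label trial, and under section 2.7 the control arm receives basic treatment with no placebo. The symptom score is the more subjective of the two primaries, and under an either-suffices rule it could carry the claim alone. The double ranking of VFA adds to the problem: if VFA missed significance, the document would support describing it as a failed primary or as an unremarkable secondary. The sample size does not settle which outcome is decisive, since it rests on neither.

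**Working it through.** **1. The passages side by side.** Sections 2.8.2 and 2.8.3 give one variable, over one interval, two incompatible ranks. The abstract repeats this in consecutive sentences. This is a contradiction within the stated outcomes and needs no arithmetic.

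**2. If either outcome suffices.** Inputs: two tests at 0.05 (section 3.1). Two-sided testing is an assumption, because neither section 2.10 nor section 3.1 states sidedness. The plan gives no family-wise figure to reproduce.

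- Independent tests: 1 − (1 − 0.05)² = 1 − 0.9025 = 0.0975.
- Correlated tests: 1 − P(|Z₁| < 1.96 and |Z₂| < 1.96), with Z₁ and Z₂ bivariate normal. The documents give no correlation, so a range is shown.

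| Assumed correlation | At least one false rejection |
|---|---|
| 0 | 9.75% |
| 0.3 | 9.5% |
| 0.5 | 9.1% |
| 0.8 | 7.8% |
| 0.9 | 7.0% |

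These figures count rejections in either direction. Counting only rejections that favour JTTF, the independent case is 1 − 0.975² = 4.94%, against 2.5% for a single test, so the relative inflation is similar. Whatever the dependence, the two-sided rate cannot exceed 0.05 + 0.05 = 10%.

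**3. If both are required.** A false claim needs rejection of at least one true null, so its probability is at most 0.05. If both nulls are true and the tests are independent, it is 0.05² = 0.25%.

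**4. Power if both are required.** This needs an effect size and SD for VFA change and for the TCM score. The document gives neither, so no figure can be derived.

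**5. Rules that would hold 5% at the final analysis.**
- Both required, 0.05 each: at most 5%, from step 3.
- Fixed sequence, 0.05 each: if the first null is true, any false claim requires its rejection, at most 0.05. If the first null is false, the only possible error is on the second, again at most 0.05.
- Holm: the smaller p-value is compared with 0.025 and, if that succeeds, the larger with 0.05. The family-wise rate is at most 5%.

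**6. The interim look.** Suppose each outcome were also tested at two-sided 0.05 at half the information, with a win then counting. By simulation, one outcome alone would have a false-positive rate of about 8.3%. With either outcome sufficing, it would be about 15.9% at correlation 0 and 14.8% at 0.5. Section 3.2 does not say that the look would be used this way. The figures show only that none of the alpha levels in step 5 can be taken at face value until the role of the look is stated.

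**The case against.** The strongest objection is that this is a condensed article. Multiplicity procedures are commonly left to a statistical analysis plan, which is not shown, and section 3.1 may be only a general significance line. That stands as far as it goes: the article does not show that error control is absent, and the finding does not rest on its absence. It does not excuse the contradictory rank of VFA, or a primary claim that the stated outcomes leave open.

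Some stronger readings are tempting but unsupported:

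- **That family-wise error nearly doubles.** A reader might infer this from two tests at 0.05. It follows only if either outcome suffices, and nothing in the document says so. The wording of section 2.8.2 equally allows a both-required reading.
- **That joint power is 72%.** This is 0.85² = 0.7225. The 85% belongs to HbA1c, which is neither primary, and the product also assumes independence.
- **That secondary item 5 is a slip for subcutaneous fat area.** Table 1 and the Discussion make this plausible. A leftover from an earlier ranking of outcomes would explain the duplicate listing just as well, and only the sponsor can say.

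It is also fair to say that no passage ranks VFA above the TCM score, and that section 2.1.1 includes symptom relief in the primary hypothesis. A fixed sequence starting with VFA is therefore one reasonable choice, not the only one. No testing rule removes expectation bias from the symptom score, and Holm would still allow a win on that score alone.

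**Conclusion.** The point holds. The document ranks VFA both primary and secondary, and it does not define what result makes the trial positive. Because the rule is undefined, so is the error rate. At the final analysis it is at most 5% if both outcomes are required. If either suffices, it is 9.75% for independent two-sided 0.05 tests, about 9.1% at an assumed correlation of 0.5, and lower at higher correlation. The sidedness and the correlations are assumptions.

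The effect on power cannot be given a number. The role of subcutaneous fat area is a question for the sponsor. An unseen analysis plan might contain a multiplicity method, but the protocol's own outcome lists would still have to be reconciled.

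**What to change.** 1. List VFA once. If it stays primary, remove it from section 2.8.3 and from the secondary outcomes in the abstract.
2. State the success rule in section 2.8.2 and carry it into section 3.1, choosing one of:
   - both outcomes required, each at 0.05;
   - a fixed sequence, with VFA change at week 12 tested first at two-sided 0.05 and the TCM score tested at 0.05 only if VFA succeeds. This order is reasonable because the symptom score is the more subjective measure in an open-label trial;
   - Holm across the two, if they are to stay equal.
3. State in section 3.2 that the interim look either carries no efficacy claim or spends part of the same 0.05.
4. Have the sponsor confirm whether secondary item 5 was meant to be subcutaneous fat area, and add that outcome only if so.

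**Cost.** No visit or measurement changes. Section 5 describes a registered trial still recruiting at submission, so the change needs a dated amendment and a registry update, preferably before any comparative results are seen. Under the fixed sequence, the TCM score has no confirmatory claim if VFA fails. Requiring both costs power by an amount that cannot be stated until effect sizes and SDs are given for the two primaries.

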**FIGURE 1 F1:**
[figure not shown]
Flow chart of the clinical trial.

**TABLE 1 T1:** Schedule of the clinical trial.

Project time	Screening/baseline		Treatment			
	-14–0 days	0±2 days	Visit 1 4weeks± 2days	Visit 2 6weeks± 4days	Visit 3 8weeks± 6days	Visit 4 12weeks± 7days
Eligibility screening						
Inclusion/exclusion criteria	**✓**					
Informed consent form	**✓**					
Allocation	**✓**					
General information	**✓**					
Family history	**✓**					
Medical history	**✓**					
Drinking history	**✓**					
Physical examination^a^	**✓**	**✓**	**✓**	**✓**	**✓**	**✓**
Vital signs^b^	**✓**	**✓**	**✓**	**✓**	**✓**	**✓**
Ultrasound of liver	**✓**					**✓**
bioelectrical impedance analysis						
visceral fat area		**✓**				**✓**
subcutaneous fat area		**✓**				**✓**
Electrocardiography	**✓**			**✓**		**✓**
Laboratory examination						
Routine blood test		**✓**		**✓**		**✓**
Routine urine test		**✓**		**✓**		**✓**
Fasting blood sugar		**✓**		**✓**		**✓**
2-h plasma glucose		**✓**				**✓**
Glycated hemoglobin		**✓**				**✓**
Fasting insulin		**✓**				**✓**
Blood lipids		**✓**		**✓**		**✓**
Liver function		**✓**		**✓**		**✓**
Renal function		**✓**		**✓**		**✓**
Traditional Chinese medicine symptoms		**✓**	**✓**	**✓**	**✓**	**✓**
Fibrosis 4 Score		**✓**				**✓**
Homeostasis model assessment-insulin resistance		**✓**				**✓**
homeostatic model assessment for β-cell		**✓**				**✓**
Metabolomics test^c^						
Serum sample		**✓**				**✓**
Urine sample		**✓**				**✓**
Adverse event			**✓**	**✓**	**✓**	**✓**
Prescription		**✓**	**✓**	**✓**	**✓**	**✓**
Combined drugs		**✓**	**✓**	**✓**	**✓**	**✓**
Summary of the analysis						**✓**

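### The TCM total score, a primary outcome scored at four post-baseline visits, has no stated deciding week and is left to an unadjusted two-sample test that uses one value per patient

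*Protocol article*

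**What the plan says.** **Primary outcomes.** Section 2.8.2 states: "The primary outcome is change in visceral fat area (VFA) and TCM syndromes efficacy score scale". The Abstract adds that the total score is meant: "The primary outcome will be change in visceral fat area and total score on the TCM syndromes efficacy score scale". Neither sentence names a week.

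**Timing within 2.8.2.** The next two sentences are: "Changes in VFA will be compared between the two groups before and after treatment. The indicator will be tested at baseline and week 12". The second is in the singular and follows a sentence about VFA. On the TCM score the section adds only: "The TCM symptom scoring standard is presented in Supplementary Material S3".

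**Visit schedule.** In Table 1 (section 2.2) the VFA row is ticked at day 0 and week 12. The row "Traditional Chinese medicine symptoms" is ticked at day 0 and at weeks 4, 6, 8 and 12.

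**Timing elsewhere.** Section 2.8.3 says "All measurements will be performed at baseline and at week 12". That line closes the list of secondary outcomes, which does not include the TCM score.

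**Analysis.** Under normality, section 3.1 says "an independent sample *t*-test will be used to assess the differences between the two groups". It also names a "paired sample *t*-test to compare the differences between groups before and after the intervention", a Wilcoxon test for non-normal data, and a Wilcoxon or CMH test for graded data. The threshold is p < 0.05. No covariate adjustment or repeated-measures method is named.

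**The concern.** The deciding week is written down for the primary outcome that has one post-baseline measurement, and not for the one that has four. The week is part of what defines a primary outcome. The article found room to give it for VFA in the same paragraph.

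The test named in 3.1 also fits this outcome poorly. A two-sample test takes one number per patient. The trial will already hold a baseline score and three interim scores, and it plans for 20% drop-out. The named test uses baseline at most by subtraction, and on observed data it uses no interim score at all.

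Two features of the trial raise the stakes. It is open-label for participants and physicians (2.9) and the score is symptom-based, so the between-arm difference may well vary over time. Section 3.2 also plans an interim analysis of the primary outcome at 50% enrolment. Patients enrolled in the preceding 12 weeks will then have only earlier TCM scores, so the visit that counts should be settled before that look.

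**Working it through.** **1. Is a week fixed for the TCM score anywhere?**

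- 2.8.2: week 12 is attached to a single indicator, directly after the VFA sentence. No week is given for TCM.
- 2.8.3: baseline and week 12, but for a list without the TCM score. Its one stated exception is FPG and lipids at week 6. Read as covering the TCM score, it would not fit the week 4, 6 and 8 ticks in Table 1.
- 3.1: the before-and-after wording points to the end of a 12-week treatment, but names neither the TCM score nor a week.

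Week 12 is therefore implied and not stated.

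**2. The plan's own figures.** The article gives no effect size, SD, error rate or power for the TCM score; section 2.10 sizes the trial on HbA1c. The only figures that bear on this point are those of the drop-out step:

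- 76 / (1 − 0.20) = 95, against 96 stated (48 per arm). This reproduces apart from one patient.

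**3. Patients whose interim scores could go unused.**

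- 96 × 0.20 = 19.2, or 96 − 76 = 20. This gives about 19 or 20 patients.
- It is an upper bound. It assumes that every drop-out has at least one score at week 4, 6 or 8 and none at week 12. Some will leave before week 4. Some who meet the compliance or prohibited-drug criteria in 2.6 may still be scored at week 12.

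**4. Exposure if the visit were left open.** Suppose there is no effect, four two-sided tests at 0.05, and success is claimed if any one is significant.

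- Ceiling under independence: 1 − (1 − 0.05)^4 = 1 − 0.8145 = 0.1855.
- For correlated visits the documents give no correlation, so a range is assumed. Simulation with 38 per arm and 40,000 runs gives:

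| Assumed correlation | Equal between all visits | Decaying with time (value at 4 weeks apart) |
|---|---|---|
| 0.5 | 0.158 | 0.151 |
| 0.7 | 0.131 | 0.130 |
| 0.8 | 0.110 | 0.112 |
| 0.9 | 0.094 | 0.093 |

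A separate simulation of four equally correlated normal statistics (1,000,000 draws) gives 0.156, 0.131, 0.114 and 0.094. The range is thus about 9% to 16%, against 5% when one visit is fixed in advance.

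**5. Precision gain from a repeated-measures model.** This depends on the SD of the TCM score and on the correlations between visits. The documents give neither, so it is not computed.

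**The case against.** **The plan does not set up four primary tests.** A reader might infer from Table 1 and the p < 0.05 rule that any of the four visits may decide the TCM outcome. The documents do not support this. The outcome is a change, the trial lasts 12 weeks, and 3.1 compares before with after the intervention, whereas weeks 4 to 8 fall during it. Section 3.1 sets one general threshold and plans no visit-by-visit testing. Scoring symptoms at each visit is ordinary monitoring. This objection stands: the first half of the point is an unstated week, not a planned any-visit rule.

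**The 18.5% ceiling is not realistic.** Scores from one patient, taken as change from one shared baseline, are not independent. This also stands, so the ceiling is shown only as a bound.

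**The two-sample t-test is not the only method named.** This is correct: 3.1 also lists a paired t-test, Wilcoxon tests and CMH. None of them combines several visits or adjusts for a baseline covariate, so the point is unaffected. The non-normal route does need a counterpart in any replacement.

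**Missing-data rules may be in an analysis plan that is not shown.** This is fair. An absent imputation rule is no finding here, and a two-sample comparison of change at the end of treatment is not in itself an error. What remains rests on what 3.1 does say: it commits a primary outcome to a test with one value per patient, when more informative data are already being collected.

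**Conclusion.** The point holds in a limited form. The TCM primary outcome lacks a stated deciding week, although week 12 is the natural reading. The named between-arm test is weaker than the data allow: it has no baseline covariate and, on observed data, makes no use of interim scores from patients without a week-12 score, at most about 19 or 20 of 96.

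The 9% to 16% range rests on assumed correlations and on free choice among the four visits. It shows what a stated week rules out. A reader might take it as the trial's actual type I error, but nothing in the article supports that. Nor can it be said that about 20 patients will be lost, or by how much precision would improve. The change is worth making, ideally before the interim analysis, but the point does not invalidate the design.

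**What to change.** **Section 2.8.2.** State that the primary TCM contrast is the between-arm difference in change in total score from baseline to week 12, and that weeks 4, 6 and 8 are supportive.

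**Section 3.1.** For this outcome, replace the two-sample test with a mixed model for repeated measures on change at weeks 4, 6, 8 and 12. Include arm, visit, arm-by-visit interaction and baseline score, with an unstructured covariance, in all randomised patients with at least one post-baseline score. Test the week-12 contrast. Keep a rank-based or similar sensitivity analysis in case residuals are clearly non-normal.

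**Cost.** A few sentences, and a standard model available in the SPSS software already named. No extra visits, patients or measurements are needed. The model assumes data are missing at random, and a benefit seen only at an early visit could not be claimed as a primary result. The change does not remove the bias that open-label assessment may bring to a symptom score.
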